**f. Does this research involve genetic testing?**

Genetic testing will not be involved in this research protocol.

**g. Does this research involve banking of information or material (blood, tissue, etc) for future use or for purposes that are not integral to the current research?**

This research involves the collection and storage of data for comparison between enrolled study subjects. This information to be collected and analyzed is data that are currently collected and stored as part of the standard clinical care that a transplant recipient receives. Gathering of this information will continue as long as the graft is functioning or until the subject passes away and may be used in future publications. This project does not involve the banking of blood, tissues, etc.

**11. Drugs and Devices**

**a. Does this study involve investigational drugs or devices (test articles)?** This study does not involve investigational drugs or devices.

**b. Does this study involve FDA approved drugs or devices used for off-label purposes?**

Yes, the FDA-approved drug Thymoglobulin will be used off-label.

**1) What is the off-label use?** Off-label use of Thymoglobulin is for immunosuppression induction.

**2) Will the results of this study be used by the manufacturer to support (a) a new indication for the drug, (b) a significant change in the labeling for the drug, or (c) a significant change in the advertising for the drug?** Based on study findings to date, the manufacturer has indicated interest in obtaining a new label indication for Thymoglobulin use as an induction agent in transplantation. Such an additional indication will require a more extensive multi-center trial for which the current study can be viewed as a pilot study.

**3) Does the study involve a route of administration or dosage level, use in a subject population, or other factor that significantly increases the risks (or decreases the acceptability of the risks) associated with the use of the drug?**

No, our study results to date indicate that the risks associated with the administration of the single rATG dose are statistically identical to the risks associated with the administration of the conventional divided-dose.

**c. Provide an FDA Use-in-Pregnancy category (A, B, C, D or X) for each drug used as a part of this research.**

The FDA Use-in-Pregnancy category for Thymoglobulin is C.

**12. Data Storage and Confidentiality**

**a. Where will the research data be stored during the study and how will it be secured?**

Research data will be collected and stored in the Department of Surgery in an office that is locked during non-business hours on computers that are password-protected. Information obtained through this research protocol will be available only to qualified investigators, the study team, representatives of the IRB, and to persons involved in the care of these patients. No patient data will be released to unqualified individuals and no data with subject identifiers will be released in reports or published.

**b. Will research data be disclosed to anyone at UNMC and The Nebraska Medical Center who is not listed in section I of the application?**

Yes, the research data may be disclosed to members of the IRB upon request.

**c. Will research data be disclosed to any investigators outside of UNMC and The Nebraska Medical Center?**

Yes, research data without patient identifiers will be disclosed to [name] of Sigma Analytics, who will be performing biostatistical analyses for us under contract.

**d. Will research data be disclosed to any commercial sponsor, contract research organization (CRO) or Data and Safety Monitoring Board (DSMB)?**

No.

**e. Will research data be disclosed to any other external organization or entity (e.g., cooperative groups, NIH, FDA, registries)?**

The research data may be disclosed to the FDA; however disclosure of this data will not include patient specific identifiers.

**f. Will research data be shared with third party payers?** No.

**g. For what duration of time will research data be subject to disclosure to the persons or groups identified above?**

The research data will be subject to disclosure for the duration of the research and until data analysis is complete.

**RISK/BENEFIT ASSESSMENT (13-19)**

**13. Potential Risks**

**What are the potential risks associated with each intervention? If data are available, estimate the probability that a given harm may occur and its potential reversibility.**

Thymoglobulin: The study drug, Thymoglobulin, works by destroying one type of the body’s white blood cells (lymphocytes) that fight against the transplanted organ as well as infection. Thymoglobulin can also cause a decrease in the number of platelets. This may increase the risk of bleeding after surgery. Investigators will monitor the number of white blood cells and platelets every day while the subject is receiving the study drug, and the Thymoglobulin dose may be adjusted if blood counts fall. The investigator may stop Thymoglobulin if they fall too low, and Thymoglobulin may be restarted once these levels come back up.

Rarely, the symptoms of serum sickness (rash, muscle aches, fever and joint pain) can occur approximately 2 weeks after therapy with Thymoglobulin. These symptoms can be treated with administration of steroids, medications that the patient will receive as part of the transplant therapy during his/her initial post transplant hospital stay.

In rare instances, the patient may experience an allergic reaction to the study medication. This occurs because he/she is receiving a foreign protein (a product produced in a rabbit). The allergic reaction may cause a difficulty in breathing, low blood pressure, and shock.

While the patient is receiving the Thymoglobulin, he/she will be monitored closely with frequent measurements of pulse, breathing, and blood pressure. Severe lung (respiratory) reactions or allergic reactions are extremely uncommon but can be potentially life threatening.

Very common adverse events occurring in greater than 10% of patients who participated in a clinical study include: decreased white blood cells, decreased platelets (needed for normal blood clotting), headache, joint pain, and back pain. Nausea, vomiting, fever, chills, and increased heart rate have also occurred which may or may not be a “first dose effect” from the initial Thymoglobulin administration. The patient will be given pre-medications prior to the administration of each dose of Thymoglobulin to minimize these symptoms.

Common adverse events occurring between 1 and 10% of patients who participated in a clinical study include: diarrhea, chest pain, tremors, shortness of breath, decreased blood pressure, decreased or lack of appetite, dizziness, itching, sweating, and hives. Rash and/or muscle aches have also occurred which may or may not be symptoms of serum sickness.

The use of Thymoglobulin may increase the risk for certain types of infections (bacterial, viral, and fungal) after transplantation. These risks may be further increased by the administration of Thymoglobulin. Types of infections reported following the use of Thymoglobulin include viral infections such as Epstein-Barr virus (EBV) infection and cytomegalovirus (CMV) infection, fungal infections such as aspergillosis, and bacterial infections. Other infections have been reported systemically in the blood or tissues.

The risk of developing certain kinds of tumors is increased after transplantation associated with the use of immunosuppression, such as is being employed in both arms of this study. Lymphomas secondary to an EBV infection are a common malignancy reported following transplant and intense immunosuppression. Other malignancies have been reported on the surface of the skin and lungs, and less commonly other organs.

Patients may experience some pain and bruising at the site where the Thymoglobulin is being injected (infusion site in vein or central line).

Side effects (adverse events) experienced by patients who have recently received Thymoglobulin commercially (outside of formal clinical trials) are the following: multi-organ failure, respiratory failure, heart attack, complications of transplant surgery, complications with normal blood clotting, allergic reaction, accumulation of excess fluid in the lungs, pneumonia (both bacterial and viral), dehydration, decreased oxygen levels in blood and tissues, complications of kidney transplant such as renal tubular necrosis, and elevations in various liver and kidney function tests. As Thymoglobulin is approved and available commercially in many countries including the US and Canada, the exact frequency of these reported events cannot be determined.

Rapamune^®^: The most common side effects of Rapamune include a temporary increase in the blood levels of liver enzymes (showing an unwanted effect on the liver), and in cholesterol and triglycerides (fat in the blood). Temporary decreases in platelets (cells that help blood to clot), white blood cells (cells that fight infection), and in blood levels of phosphorus and magnesium have also occurred.

Some patients have also developed nose-bleeds, headache, indigestion, diarrhea, irritation of the mouth, anemia, night sweats, decreased male hormone, joint pain, infections, elevation of blood pressure, acne, rash, abnormal collection of lymph fluid around the transplanted kidney (lymphocele), fever, and bleeding abnormalities.

All patients will receive the standard medications needed to prevent the common infections after kidney transplant. Risk of monotherapy with Rapamycin could increase the risk of rejection in the transplanted organ.

Prograf^®^: The most common adverse effects of Prograf reported in kidney transplantation are tremor, headache, diarrhea, constipation, abdominal pain, high blood pressure, decreased kidney function, infection and insomnia. Other side effects that may occur with Prograf include numbness or tingling usually of the hands and feet, nausea and vomiting, lowered blood magnesium, decrease in the red blood cells, urinary tract infection, muscle weakness, shortness of breath, pain, fever, swelling, and skin rash or itching. Some patients may also experience elevated blood sugar levels and some of these patients will require insulin to control their blood sugar levels.

CellCept^®^: The principal adverse reactions associated with the administration of CellCept include diarrhea, leukopenia, sepsis, and vomiting. There is also evidence of a higher frequency of certain types of opportunistic infections.

Anti-rejection (immunosuppressant) medication: Other possible side effects associated with anti-rejection medicines are shortness of breath, itching or rash on the skin, fever or back pain.

The risk of developing certain types of tumors (cancer) after transplantation may be increased with the use of any of the anti-rejection medicines that are being used for all patients participating in this study.

Kidney biopsies: Kidney biopsies can be painful where the needle enters the body, and a bruise can form. Bleeding can occur where the needle is inserted into the kidney. Blood can appear in the urine.

Drawing blood: The usual risks of drawing blood include pain, possibility of infection, perforation of the vein, bruising, and/or discoloration or bleeding from the place where the needle was inserted. There is also a slight possibility of the formation of a blood clot or that you might feel faint. There is no additional risk when an extra tube of blood is drawn at the time of a routine blood draw.

Randomization: When patients are randomized to different groups, there is the risk that patients in one group will not do as well as patients in the other group. In this study, that could mean that one group may have a higher risk of developing rejection of the transplanted kidney than another group.

Pregnancy: Adequate, well-controlled human studies are lacking. Therefore, there may be risk to a fetus if these drugs are administered during pregnancy (FDA Use-in-Pregnancy Category C).

Unknown risks: The drugs used in this study may also involve risks that are not yet known.

**14. Risk Classification**

**What is the overall risk classification of the research: minimal risk, greater than minimal risk but less than significant risk, or significant risk?**

The risk classification is significant due to the nature of kidney transplantation and the continuing requirement for immunosuppression to preserve the graft.

**15. Data and Safety Monitoring**

**a. How will subject safety be assessed on an ongoing basis throughout the study?**

All subjects will be scheduled for follow up visits as outlined previously, which is standard practice in renal transplant. Investigators and participating healthcare providers will be present at the follow-up visits. Additionally, post-transplant coordinators will be following subjects, as is standard practice, through phone calls and other communications. Laboratory tests and biopsies performed at the various visits throughout the study will also allow for assessment of subject safety.

**b. What specific procedures will be utilized to prevent or minimize potential risks or discomforts associated with study interventions and procedures?** Thymoglobulin^®^; Prograf^®^; Rapamune^®^: CellCept^®^. Participants will be monitored closely for infections, malignancies, and any other adverse reactions.

Kidney biopsies: Precautions typically taken to minimize the risks of a biopsy include obtaining the following tests prior to the biopsy: a complete blood count, coagulation factors, renal ultrasound, and urinalysis. In addition, the biopsy is performed under the guidance of ultrasound.

To prevent bleeding at the site after the biopsy, patients are required to remain in bed for 6 hours and to lay for 4 hours following the procedure. A 5 lb. sandbag is placed over the site. Patients are closely observed and vital signs are checked regularly during this time.

Drawing blood: All usual precautions will be taken.

Randomization: All groups of subjects will receive standard maintenance therapy of tacrolimus and rapamycin in the early post-transplant period (i.e. to month 6). Only those randomized to groups 3 and 4 who have not experienced rejection and who are able to maintain rapamycin trough levels of 8 ng/ml or greater, will be transitioned to rapamycin and mycophenolate mofetil.

Pregnancy: All sexually active participants are required to practice two methods of medically acceptable birth control as long as they are on study medication and for 3 months following the discontinuation of study medication. For female subjects, pregnancy tests will be done prior to start of study medication, and if a pregnancy occurs, the participant will be withdrawn from the study.

Unknown risks: Participants are instructed to report any and all symptoms or reactions to the investigator or study staff. If side effects are unacceptable, the participant may be withdrawn from the study.

Other precautions: Procedures utilized to minimize risk include provision to the subject of contact phone numbers for coordinators and study personnel, administration of tests or interventions by qualified personnel, and the use of procedures and medications to reduce known side effects.

**c. What are the specific subject withdrawal criteria?**

Criteria for subject withdrawal from this study include:

- Withdrawal of consent by the subject at any time during the course of the study
- Second transplant after initial kidney transplant (i.e. pancreas and liver)
- Graft loss
- Subject is lost to follow-up
- Pregnancy
- Patient experiences an unmanageable adverse event
- Death of subject
- Study is terminated

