**8. Inclusion Criteria**

**What are the specific inclusion criteria?**

- 1. Primary renal transplant recipient
  2. Recipient of a re-transplant, if:
- previous graft(s) lost due to non–immunological factors, ***or***
- previous graft(s) lost due to immunological factors, but while maintained on the less-effective immunosuppression agents of the previous era, i.e., cyclosporine, steroids, and/or azathioprine
  1. Cadaveric donors
  2. Living renal donor
  3. Recipient of renal transplant with planned pancreas transplant at a later date
  4. Zero-mismatch human leukocyte antigen donors

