- Transglutaminase expression will be measured 1 hr post-initiation of first dose of rATG.

● Serum levels of ε (γ-glutamyl)-lysine diisopeptide will be measured every other day for 7 days post-transplantation then weekly until pre-transplant levels are reached.

● TREC output will be measured weekly, until levels return to baseline, beginning 2 days post-completion of rATG therapy.

● CD3 counts will be measured daily until total counts are > 100.

● Gene array analyses for assessment of functional signal transduction pathways and analysis of cell surface phenotypes of peripheral blood leukocytes will be performed at 1, 3, 6, and 12 months post-transplantation.

All participants will follow the standard post-transplant schedule for routine laboratory testing.

For safety purposes, subjects will have surveillance biopsies at 6, 12, and 24 months. If future funding becomes available, a renal biopsy at year 5 may be added. (If this becomes feasible, the protocol will be amended and an addendum consent form will be prepared for the subjects.) Subjects who present with a condition, either medically or anatomically, that would present a greater risk to the subject, may at the discretion of the Principal Investigator forego a kidney biopsy. Banff scoring will be utilized to categorize rejection and transplant nephropathy. It is standard practice at this center to request surveillance biopsies for renal transplant recipients who are not receiving steroids as part of their maintenance immunosuppression.

Participants will return for study visits at 1, 3, 6, 12, and 24 months and as needed in accordance with standard schedule for all transplant patients. Long-term data regarding graft and patient survival, incidence of allograft rejection, serious adverse events, CMV disease, opportunistic infections, PTLD, hyperlipidemia, wound healing problems, lymphoceles and immunosuppression regimen will be collected at years 3, 4, and 5 from a review of the subject’s medical record.

Adverse Events:

All adverse events will be monitored and recorded. These will include both events related to the safety profile of the study drugs (CMV disease, Post-Transplant Lymphoproliferative Disorder [PTLD], opportunistic infections, elevated lipids, etc.) and expected renal transplant complications (wounds, lymphoceles, diabetes, weight gain, etc.). All unexpected adverse events and any deaths will be reported to the IRB per UNMC policies.

Endpoints:

Primary endpoints:

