3. PTLD

4. Hyperlipidemia

5. Wound healing problems

6. Lymphoceles

1. Requirement for additional immunosuppression (such as corticosteroids, antimetabolites or other immunosuppressive agents)
2. Acute rejection per kidney biopsy (Banff grading criteria)
3. ATN (acute tubular necrosis) rate (requirement for dialysis within 7 days post-transplant)
4. Graft survival
5. Patient survival
6. Immunological parameters
7. New onset BK virus per kidney biopsy
8. **Describe the follow-up of subjects and identify any procedures that are performed exclusively for research purposes, or performed more frequently than would normally be clinically indicated (e.g. additional or more frequent radiologic evaluations).**

All participants will follow the standard post-transplant schedule for routine laboratory testing.

For safety purposes, subjects will have surveillance biopsies at 6, 12, and 24 months. The renal biopsy at 24 months following transplant is performed exclusively for research purposes. Subjects who present with a condition, either medically or anatomically, that would present a greater risk to the subject, may at the discretion of the Principal Investigator forego a kidney biopsy. It is standard practice at this center to request surveillance biopsies for renal transplant recipients who are not receiving steroids as part of their maintenance immunosuppression.

Participants will return for study visits at 1, 3, 6, 12, and 24 months and as needed in accordance with standard schedule for all transplant patients. Long-term data regarding graft and patient survival, incidence of allograft rejection, serious adverse events, CMV disease, opportunistic infections, PTLD, hyperlipidemia, wound healing problems, lymphoceles and immunosuppression regimen will be collected at years 3, 4, and 5 from a review of the subject’s medical record.

To measure the long-term effect of rATG, CD3 and CD4/CD8 counts with ratio will be done at baseline, two weeks post transplant, 1, 3, 6, 12, and 18 months, and annually to year 5. These tests are performed for research purposes.

Participants may be asked to have this additional blood drawn in order to test for certain immunological parameters. This will depend on whether or not the patient is able to return to the transplant center at the required intervals. The investigator, in consultation with the patient and the study coordinator, will determine if this is possible.

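### Subjects are withdrawn from the study at graft loss, second transplant, pregnancy or an unmanageable adverse event, and nothing in the protocol keeps them in follow-up for the survival, rejection and safety endpoints

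*Protocol*

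**What the plan says.** Item 15.c of the protocol is introduced by "Criteria for subject withdrawal from this study include". Its list includes graft loss, "Second transplant after initial kidney transplant (i.e. pancreas and liver"), pregnancy and "Patient experiences an unmanageable adverse event". Withdrawn consent, loss to follow-up, death and study termination are on the same list. Item 15.b repeats that a pregnant participant is withdrawn from the study. For side effects it is permissive: "If side effects are unacceptable, the participant may be withdrawn from the study".

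Item 8 makes eligible a "Recipient of renal transplant with planned pancreas transplant at a later date".

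The secondary endpoints in item 10 include graft survival, acute rejection, a safety profile and "Patient survival". Item 10 also plans to collect "Long-term data regarding graft and patient survival, incidence of allograft rejection" and most of the safety outcomes at years 3, 4 and 5 by reviewing the medical record.

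Item 10.g, on banking of information, says: "Gathering of this information will continue as long as the graft is functioning or until the subject passes away".

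**The concern.** The list in 15.c mixes three kinds of event: endpoints (graft loss, death), administrative endings (consent, loss to follow-up, termination) and clinical events after which the endpoints can still occur (second transplant, pregnancy, adverse event). All carry the same consequence, withdrawal from the study. Because death and loss to follow-up are among them, the list reads as leaving the study, not as stopping a drug.

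If a site applies this as written, follow-up for endpoints planned to year 5 ends at events that may be related to those endpoints. Item 10.e names Kaplan-Meier estimates and log-rank tests for graft survival and acute rejection. These are valid when subjects who are censored have the same later risk as comparable subjects who remain. A subject who leaves for an adverse event that could not be managed may well not. The trial is unblinded, the word unmanageable is not defined, and only Groups 3 and 4 are assigned to leave the tacrolimus-sirolimus combination, which the background says not all patients tolerate. Such exits could therefore differ between arms.

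There is also an inconsistency between items 8 and 15.c: a subject enrolled with a pancreas transplant in prospect meets a withdrawal criterion if that transplant takes place.

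**Working it through.** This is mainly a comparison of passages.

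**Step 1. What each exit shows and what it can hide.** Triggers are from item 15.c, endpoints from item 10.

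| Exit | Observed at exit | Can be lost afterwards |
|---|---|---|
| Graft loss | The graft-loss event | Death; later infections, PTLD and other safety events |
| Second transplant | No kidney endpoint | Rejection, graft loss, death, later safety events |
| Unmanageable adverse event | That event | Rejection, graft loss, death, later safety events |
| Pregnancy | No kidney endpoint | Rejection, graft loss, death, later safety events |
| Death | The death | Nothing |

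The graft-loss event therefore stays in the graft-survival analysis, and a death that is itself the exit stays in patient survival. The gap lies in patient survival after graft loss, and in all later outcomes after the other three clinical exits.

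**Step 2. Does another passage close the gap?**
- The year 3-5 record review excludes no one explicitly, but does not say that it covers withdrawn subjects.
- Item 10.g gives two end points for data gathering joined by *or*: graft function or death. One reading stops at graft loss and the other continues to death. It neither confirms nor secures follow-up between the two.
- Item 10.e does not say how withdrawn subjects are counted. A statistical analysis plan may do so, but it cannot analyse events that were never collected.

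**Step 3. Does the drop-out allowance cover it?** Item 3.b gives the only relevant figure: 200 subjects, said to compensate for 10% drop-out. If the 180 in item 10.a is read as the evaluable number (an assumption), the figure reproduces: 180 / (1 - 0.10) = 200, an allowance of 200 x 0.10 = 20 subjects. This replaces numbers. It does not correct exits that depend on outcome.

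**Step 4. Size.** A bias estimate needs withdrawals by reason and arm, and event rates after withdrawal. The protocol gives none of these, nor the number of planned pancreas recipients. No estimate can be derived from the document.

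**The case against.** The strongest reply is that 15.c is only an end-of-participation list. It does not say that data collection stops, and the record review at years 3-5 excludes nobody. Side-effect withdrawal is permissive in item 15.b. Item 19.b reports that an interim analysis of 142 patients detected no difference in patient or graft survival. Handling of GFR after graft loss and rules for censoring commonly belong in an analysis plan, which is not shown.

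Much of this stands, and it rules out several stronger readings that a reader might infer:

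- *That failures vanish from the data.* Graft loss and death at exit are observed and can be counted.
- *That item 10.g proves collection ends at graft failure.* Its wording is ambiguous.
- *That planned pancreas recipients are certain withdrawals.* The transplant may never happen, or may fall after follow-up.
- *That the GFR contrast is shifted by a known amount.* With assumed graft loss of 5% against 10%, an assumed mean GFR of 55 in retained subjects of both arms, and failed grafts scored at 10 or 0, one gets 0.05 x (55 - 10) = 2.25 to 0.05 x (55 - 0) = 2.75 ml/min. None of these inputs is in the document. The sum compares retained subjects with all randomised subjects, whereas the planned repeated-measures mixed model uses each subject's earlier GFR values. Scoring a lost graft at a fixed value is also one choice of estimand among several. It is no measure of bias in the planned analysis.
- *That censoring does differ by arm.* There is a plausible mechanism but no evidence of it here.

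What does not stand is that nothing needs changing. A rule that withdraws subjects from the study, with no statement that their outcomes are still collected, can be followed literally. The interim result does not settle the matter: failing to detect a difference is not equality, and the result is reported for the two rATG regimens, not for calcineurin-inhibitor withdrawal.

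**Conclusion.** The point holds in a limited form. Item 15.c ends study participation at graft loss, second transplant, pregnancy or an unmanageable adverse event, and no passage keeps these subjects in outcome follow-up, although survival, rejection and safety are endpoints with most data planned to year 5. Deaths after graft loss, and rejection, graft loss and death after the other exits, can be missed, so censoring may be informative. Items 8 and 15.c also conflict for planned pancreas recipients.

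The size and direction of any bias are unknown. The conclusion rests on reading withdrawal from the study at face value. If the site in fact continues record review after withdrawal, the defect is one of wording only, but the protocol does not say so. It should be corrected. It does not by itself invalidate the primary comparisons.

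**What to change.** Reconcile items 8, 10 (follow-up and years 3-5), 10.g and 15.c by separating two things that 15.c now merges: the end of study participation or procedures, and the end of outcome follow-up. State that:

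1. every subject except those withdrawing consent stays in the existing medical-record follow-up for graft loss, rejection, serious adverse events and death to year 5;
2. these events are counted in the randomised group, without censoring at a second transplant or an adverse-event exit;
3. collection under item 10.g continues after graft loss, so that patient survival is complete.

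How GFR is handled after graft loss can be left to the analysis plan.

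The record review already exists, so the added work is modest. There are two costs. Some follow-up will include time off the assigned regimen. Subjects already enrolled or withdrawn may also need an addendum consent, since item 29 shows that earlier changes, including extended follow-up, were handled that way. Outcomes of subjects withdrawn before the change may be only partly recoverable. The change concerns data collection and counting only; no change to treatment or clinical management is proposed.
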